**Methods:**

The primary aim of this study is to determine the effect of family-administered delirium prevention, detection, and management in critically ill patients on family member symptoms of depression and anxiety, compared to usual care. One-hundred and ninety-eight patient-family dyads will be recruited from four medical-surgical ICUs in Calgary, Canada. Dyads will be randomized 1:1 to the intervention or control group. The intervention consists of family-partnered delirium prevention, detection, and management, while the control group will receive usual care. Delirium, depression, and anxiety will be measured using validated tools, and participants will be followed for 1- and 3-months post-ICU discharge. All analyses will be intention-to-treat and adjusted for pre-identified covariates. Ethical approval has been granted by the University of Calgary Conjoint Health Research Ethics Board (REB19–1000) and the trial registered. The protocol adheres to the Standard Protocol Items: Recommendations for Interventional Trials (SPIRIT) checklist.

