Despite high prevalence, detrimental effects, and priority as a quality improvement initiative, delirium is often overlooked in the ICU or assumed to be a normal part of a patients’ clinical course [31]. The importance of brain dysfunction in the ICU is increasingly recognized and although formal delirium screening programs have been implemented worldwide, the majority of cases remain undetected [31]. Family members may be able to notice subtle changes in patients’ cognition and behavior before an unfamiliar clinical observer [32]. The prevention and management of delirium is also challenging; the only guideline recommended therapies for delirium are non-pharmacological and there are presently no known effective pharmacotherapies for delirium [33]. Family members may be engaged in these non-pharmacological delirium prevention and management therapies at the bedside through activities such as re-orientation, familiarization, and mobilization [33]. Critically ill patients are frequently unable to participate in their own care; by partnering with their family members (e.g., immediate family, relatives, friends), we may be able to improve experiences and outcomes of care for both patients and families [10, 34, 35]. We hypothesize that structured engagement of family members in the detection of delirium symptoms and prevention and management of delirium using non-pharmacological strategies will decrease the number of symptoms of anxiety and depression in family members of critically ill patients and may decrease the duration and severity of delirium in critically ill patients.

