### Randomization

Participants will be randomized using computer-generated randomization to either the intervention group or the control group (1:1). Randomization will be stratified by site and restricted using permuted random blocks within each strata. The random allocation sequence will be implemented using the REDCap study database by a biostatistician unaffiliated with the study. This biostatistician will generate the random allocation sequence to assign participants to either the intervention or control groups. No one directly involved in the study will have access to the allocation sequence and this feature will be accessed exclusively by the unaffiliated biostatistician. The pre-determined allocation sequence from the biostatistician will be employed centrally (FMC) to assign participants to the intervention or control group. Research assistants will receive this information from the REDCap database once a patient is consented.

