### Statistical analysis plan

All data will be analyzed as intention to treat. Descriptive statistics will be used to summarize the patient and family characteristics. For all analyses, we will consider a two-tailed *p*-value < 0.05 to be statistically significant, and will adjust for multiple comparisons (Bonferroni correction) in the primary analysis where appropriate. For the secondary aims, we will not correct for multiple comparisons with statistical procedures, but rather consider them in our interpretation. Subgroup analyses and a priori *covariates* to be considered are: presence of mechanical ventilation, RASS score, delirium subtype, patient frailty status (based on Clinical Frailty Scale scores), patient age, patient sex, caregiver age, caregiver sex, and baseline levels of symptoms of depression, anxiety, and psychological distress. Linear regression models will be used to assess for effect modification and confounding. Missing data will be tabulated for all outcomes. If more than 5% of outcome data is missing, multiple imputation will be employed; for the primary aim, we will also conduct a sensitivity analysis assuming the data is missing not at random.

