For the primary aim, we will report a difference in proportion of the clinically significant symptoms of depression [PHQ-9] and anxiety [GAD-7], mean PHQ-9 and GAD-7 scores, and frequency of categories of depression and anxiety (i.e., minimal, mild, moderate and severe) (at discharge from ICU, 1-, and 3- month follow-up) between control and intervention groups. For secondary aims we will report: 1) A difference in proportion of the most severe family members symptoms of psychological distress [K-10] (at discharge from ICU, 1-, and 3- month follow-up) between control and intervention groups. 2) Prevalence of delirium: Difference in proportion of patients with clinical delirium (ICDSC score ≥ 4) pre-post intervention (in-ICU) between control and intervention groups. Duration of delirium: Difference in mean days with clinical delirium (ICDSC score ≥ 4) pre-post intervention between control and intervention groups (in-ICU). Duration of delirium-free days: Difference in mean days without delirium on the ICDSC pre-post intervention between control and intervention groups (in-ICU). Severity of delirium: Difference in most severe ICDSC scores pre-post intervention between control and intervention groups (in-ICU). 3) Difference in the diagnosis of delirium in the medical chart, compared to usual care (when appropriate, i.e., when delirium is present) pre-post intervention between control and intervention groups (in-ICU). 4) Difference in mean CIDKQ scores pre-post intervention between control and intervention groups (in-ICU). 5) Difference in mean DEL-B scores pre-post intervention between control and intervention groups (in-hospital). The statistical significance of the differences between proportions or means (between the intervention and control groups) will be calculated using the.

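### The covariate and subgroup list includes delirium subtype with no time point and no coding for patients without delirium, and leaves out site, the stratification factor

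*Protocol article*

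**What the plan says.** The Statistical analysis plan section of the protocol article gives one list that serves both subgroup analyses and covariates to be considered. It opens with "presence of mechanical ventilation, RASS score, delirium subtype, patient frailty status" and goes on to "patient age, patient sex, caregiver age, caregiver sex, and baseline levels of symptoms of depression, anxiety, and psychological distress". The word baseline qualifies only the symptom scores. No time point is given for subtype, RASS or ventilation, no category is given for a patient without delirium, and site is not listed.

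The same section adds: "Linear regression models will be used to assess for effect modification and confounding". The Methods paragraph of the Abstract is firmer about use: "All analyses will be intention-to-treat and adjusted for pre-identified covariates".

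On the design side, the Randomization section says: "Randomization will be stratified by site and restricted using permuted random blocks within each strata". Table 1 asks for a RASS score of at least -3 but not for delirium, and dyads may join at any time in the ICU stay. The Background hypothesises that the intervention "may decrease the duration and severity of delirium in critically ill patients". The secondary comparisons include "Prevalence of delirium: Difference in proportion of patients with clinical delirium", together with duration and severity. Table 2 marks ICDSC and RASS both at baseline and daily.

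**The concern.** A patient who is not delirious at entry can acquire a subtype only after randomisation, under an intervention meant to change whether and how delirium develops. The Background also says that seeing delirium distresses families. On the protocol's own reasoning, in-ICU delirium may therefore lie on the path from the intervention to the family's depression and anxiety scores. Conditioning on it removes that part of the effect from the estimate. It also compares groups that are no longer balanced by randomisation, whether it is done by adjustment or by subgroup.

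Two further problems follow from the missing coding. For the secondary aim on delirium prevalence, an in-stay subtype exists only when the outcome is yes, so it cannot serve as a covariate. And if patients without delirium have no value, a complete-case model leaves them out.

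Site is a separate and smaller matter. The design balances on it, and an explicit covariate list then omits it.

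**Working it through.** **The plan's own figures.** The Sample size calculation section uses a 3-point difference, SD 5, 90% power, alpha 0.05 (two-sided by the analysis section) and 20% loss.
- Primary: the t-test needs 59.35, so 60 per group; 60 x 1.2 = 72, as stated.
- Secondary (10% against 30%): the pooled formula gives 82, and 82 x 1.2 = 98.4, so 99. The unpooled formula gives 79, and 79/0.8 = 98.75, also 99.

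Both figures reproduce, and neither depends on the covariate list. With 99 per group and 20% loss, about 99 x 0.8 = 79 per group are analysed.

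**Starting power.** SE = 5 x sqrt(2/79) = 0.796. Power = Phi(3/0.796 - 1.96) = Phi(1.81), about 96%.

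**Case A: subtype taken during the stay, with none as a category.** Let the intervention lower the probability of delirium by d from an assumed 50%, and let delirium add g points to the family score. Both are assumptions. With a total effect of -3, the part not passing through delirium is -3 + d x g, and that is what the adjusted model estimates.

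| d | g | -3 + d x g | Simulated mean, adjusted |
|---|---|---|---|
| 0.10 | 2 | -2.8 | -2.76 |
| 0.10 | 4 | -2.6 | -2.57 |
| 0.20 | 2 | -2.6 | -2.59 |
| 0.20 | 4 | -2.2 | -2.20 |

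The simulations used 158 dyads, a residual SD of 5, two subtypes plus none, and 2,000 runs per row. Unadjusted means were -2.96 to -2.99. The loss is 0.2/3 = 7% to 0.8/3 = 27% of the effect. If d or g is zero, nothing is lost by this route.

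**Case B: subtype blank without delirium, and complete-case models.** Neither is stated in the article. Let p be the share of patients with a subtype, so n = 79p per group and power = Phi(3/(5 x sqrt(2/n)) - 1.96).

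| p | n per group | SE | Power |
|---|---|---|---|
| 0.3 | 23.7 | 1.453 | 54% |
| 0.5 | 39.5 | 1.125 | 76% |
| 0.6 | 47.4 | 1.027 | 83% |

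The Background puts delirium in more than half of ICU patients. The lower rows allow for a smaller share within a study window of at most five days, which is again an assumption.

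**Case C: ever/never delirium as the outcome.** With an in-stay subtype and a none category, none predicts the outcome perfectly. With blanks, every remaining patient has the outcome. In either case no treatment effect can be estimated sensibly.

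**Site.** Four sites were sized in proportion to beds (28, 18, 10, 10, giving 67, 43, 24 and 24 of 158), with an assumed site share of outcome variance of 0 to 10% and 4,000 runs each.

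| Site share | Type I error without / with site | Power without / with site |
|---|---|---|
| 0 | 5.7% / 5.7% | 95.9% / 95.9% |
| 2% | 4.7% / 4.8% | 96.8% / 96.9% |
| 5% | 3.9% / 4.2% | 97.3% / 97.4% |
| 10% | 4.3% / 4.9% | 97.3% / 97.7% |

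The differences between models are well under one percentage point. At a 5% share, the SE without site is too large by a factor of about 1/sqrt(0.95) = 1.026.

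**The case against.** Subtype is not named as an outcome anywhere, and a baseline reading is possible: ICDSC and RASS are recorded at baseline, and patients recruited late in the stay may already be delirious. The list is also one of items to be considered, not a fixed model, and the article condenses a fuller plan that may settle timing and coding. This rules out saying that the trial will adjust for a post-randomisation outcome. It does not remove the point. The article attaches baseline to some items and not to subtype, and its Abstract says that all analyses are adjusted. Even a baseline subtype needs a category for eligible patients without delirium.

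A reader might infer three stronger things that the documents do not support.
- **A certain breach of intention to treat.** This requires both blank coding and complete-case fitting, and neither is stated.
- **Data-driven choice of confounders.** The sentence "Linear regression models will be used to assess for effect modification and confounding" is loose, but it gives no selection rule, and the covariates are called a priori and pre-identified.
- **Neglect of baseline ICDSC.** The delirium comparisons are framed as pre-post, which at least partly uses status before the intervention.

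On site, the four ICUs share a region, room structure, visiting policy and standard of delirium care. Any between-site difference may be small, and leaving site out errs mostly on the conservative side. That stands.

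**Conclusion.** The point holds as a defect of specification. Subtype sits in an explicit covariate and subgroup list without a time point or a code for patients without delirium, and site is missing although randomisation is stratified by it. RASS and ventilation share the missing time point. They have a simpler remedy, and for RASS a baseline record is already scheduled.

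The harm depends on how the list is applied. If subtype is taken during the stay and adjusted for, an assumed fall in delirium of 10 to 20 points and an assumed 2 to 4 points per delirium case shrink a true -3 to between about -2.8 and -2.2. The prevalence model would then have no usable form. The fall in power from about 96% to 54-83% applies only under the assumed blank coding and complete-case fitting. If subtype was always meant as a baseline value with a none category, neither harm arises and only the wording is at fault. The omission of site is a matter of consistency with the design, with a small expected gain in precision from adding it. This should be fixed, but it does not invalidate the design or the sample size.

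**What to change.** - State that every adjustment covariate and subgroup variable, including RASS and ventilation, is the value at or before randomisation.
- Replace delirium subtype with baseline delirium status, including a category for no delirium. Alternatively, take subtype out of the models and subgroups and report it descriptively by group.
- Add site to the models.

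The cost is a few lines of text, to be settled before any outcome data are compared by group. Baseline ICDSC and RASS are already in Table 2, and site is known for every dyad. Table 2 has no separate entry for ventilation, so its baseline source in the clinical information system should be confirmed. The sample size does not change.

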## Methods

### Study design

We will conduct a multicenter, non-inferiority randomized controlled trial with participants randomly assigned to family-partnered delirium prevention, detection, and management or control (standard patient care). Patients and family members will be recruited from four medical-surgical ICUs located in four hospitals (Foothills Medical Centre [FMC], Peter Lougheed Centre [PLC], Rockyview General Hospital [RGH], South Health Campus [SHC] within a publicly funded healthcare system (Alberta, Canada). FMC (28-beds), PLC (18-beds) and RGH (10-beds) are teaching hospitals, while SHC (10-beds) is a non-teaching hospital. All four ICUs are within the same health region, have the same bed structure (single bed, private room), open visitation policies and standard of delirium care. The research team has access to eCritical MetaVision, a population-based, bedside clinical information system which captures in real time demographic, clinical, and outcome data for all ICU patients in Alberta, including routinely collected clinical measures of delirium and sedation [40]. Patient demographics (e.g., birthdate, sex) and clinical characteristics (e.g., admitting SOFA and APACHE-II scores, ICDSC and RASS assessments, sedation, etc.) will be collected.

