#### Sample size calculation

*Primary Outcome:* To find a difference in the mean score on the PHQ-9 or GAD-7 of 3-points (from 13 to 10), with a standard deviation of 5-points, power of 90%, an alpha level of 0.05, and 20% loss to follow-up (based off of previous mortality rates in the study ICUs [local data]), 72 dyads per group are required (*N* = 144). *Secondary Outcomes:* To find a difference in the proportion of delirium events reported in the medical chart (most conservative estimate based on secondary outcomes selected) of 20% (from 10 to 30%) at 90% power, an alpha level of 0.05, and 20% loss to follow up, 99 dyads per group are required (*N* = 198). The primary outcome requires a smaller sample size, and thus the most conservative number based on a secondary outcome is employed here.

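### Admitting SOFA and APACHE-II are collected but absent from the a priori covariates; adding one score could sharpen the continuous patient delirium comparisons at almost no cost (minor)

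*Protocol article*

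**What the plan says.** In the protocol article, the Statistical analysis plan section gives one list that serves both subgroup analyses and covariate adjustment. Its patient part is "presence of mechanical ventilation, RASS score, delirium subtype, patient frailty status (based on Clinical Frailty Scale scores), patient age, patient sex", and its family part is "caregiver age, caregiver sex, and baseline levels of symptoms of depression, anxiety, and psychological distress". The abstract's Methods paragraph makes the adjustment general: "All analyses will be intention-to-treat and adjusted for pre-identified covariates".

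The Study design section names the bedside clinical information system as a source that "captures in real time demographic, clinical, and outcome data for all ICU patients in Alberta", and says that "clinical characteristics (e.g., admitting SOFA and APACHE-II scores, ICDSC and RASS assessments, sedation, etc.) will be collected".

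On missing data, the analysis section says "If more than 5% of outcome data is missing, multiple imputation will be employed". It names no variables for the imputation. For the primary aim it adds a sensitivity analysis under a not-at-random assumption.

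**The concern.** Two admission scores that summarise acute illness severity are available for the trial, and the list of adjustment variables contains neither. Secondary aim 2 compares days with delirium, delirium-free days and the most severe ICDSC score between arms during the ICU stay. A severity score is a plausible predictor of all three. Randomisation is stratified by site only, so the design does not balance severity between the arms.

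An outcome predictor left out of the model leaves its share of the outcome variance in the error term. Chance imbalance on it also goes unadjusted. Precision in the aim 2 comparisons is what is at stake. The omission is worth raising before the analysis because a score added after the data have been seen would no longer be pre-identified.

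**Working it through.** **1. The two lists side by side.** Study design: SOFA, APACHE-II, ICDSC, RASS and sedation are among the data collected. Analysis plan, patient covariates: ventilation, RASS, delirium subtype, frailty, age and sex. RASS appears in both; SOFA and APACHE-II appear only in the first.

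**2. The plan's own sample sizes reproduce and do not depend on this point.**
- Chart-reported delirium, 10% against 30%, two-sided alpha 0.05, power 90%, pooled variance under the null: n = [1.960 × √(2 × 0.20 × 0.80) + 1.282 × √(0.10 × 0.90 + 0.30 × 0.70)]² / 0.20² = 82 per group. Then 82 × 1.2 = 98.4, rounded up to 99, as stated.
- PHQ-9 or GAD-7, difference 3, SD 5: the t-based n is 60 per group, and 60 × 1.2 = 72, as stated.

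Neither calculation assumes covariate adjustment, so adding a covariate changes neither figure.

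**3. Effect on a continuous aim 2 outcome.** Let R² be the share of the variance remaining after the listed covariates that the added score explains. The documents give no value; 0.05 to 0.15 is an assumption. With n = 99 per group and SD meaning the residual SD after the listed covariates:
- standard error ratio = √(1 − R²)
- equivalent n per group = 99 / (1 − R²)
- smallest difference detectable with 90% power = (1.960 + 1.282) × √(2(1 − R²)/99), in SD units
- power of a contrast that has 90% without the score = Φ(3.242/√(1 − R²) − 1.960)

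| R² | SE ratio | Fall in SE | Equivalent n per group | Detectable difference (SD) | Power from 90% |
|---|---|---|---|---|---|
| 0 | 1.000 | 0% | 99 | 0.461 | 90% |
| 0.05 | 0.975 | 2.5% | 104 | 0.449 | 91% |
| 0.10 | 0.949 | 5.1% | 110 | 0.437 | 93% |
| 0.15 | 0.922 | 7.8% | 116.5 | 0.425 | 94% |

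With 20% fewer patients (99 × 0.8 ≈ 79 per group) the detectable difference runs 0.516, 0.503, 0.489 and 0.476 SD. The ratios are unchanged.

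**4. Downside.** If the score explains nothing more, the model loses one residual degree of freedom out of somewhat fewer than 198. That is about 1/198 ≈ 0.5% of the variance.

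**5. Limits of the formula.** It holds for linear models of continuous outcomes. Delirium prevalence in aim 2 and chart diagnosis in aim 3 are binary, so the equivalent sample sizes above cannot be read across to them.

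**The case against.** The strongest reply is that nothing here is wrong. Choosing some prognostic covariates over others in advance is legitimate, and omitting one does not bias a randomised comparison. That stands, and it is why the point is minor.

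Several further arguments shrink the likely gain:
- Ventilation and RASS describe the patient's current state, and frailty and age are also listed. It would be too strong to say that the list ignores severity.
- Recruitment may happen at any time in the ICU stay, so an admission score may be out of date at randomisation.
- The eligibility rules (RASS at least −3, exclusion for Glasgow Coma Scale below 9) narrow the severity range.
- The article gives no completeness figure for the scores, only that the system covers all ICU patients in Alberta.

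All of these stand as reasons to expect the low end of the range or less. None shows that adding the score would do harm, and no other part of the article supplies it.

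A reader might also infer that the multiple imputation leaves out severity, because the sample size section assumes "20% loss to follow-up (based off of previous mortality rates in the study ICUs [local data". The documents do not support that. The article names no imputation model, and nothing says that the adjustment list doubles as one; such detail commonly sits in the statistical analysis plan. Mortality is also not the only stated source of missing data: the Discussion names the timing and availability of family members.

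**Conclusion.** The point holds as a minor improvement in precision for the continuous patient delirium outcomes of aim 2. Under an assumed further R² of 5% to 15%, the standard error falls by about 2.5% to 8%, and power of 90% becomes about 91% to 94%. The gain may be near zero, because the listed covariates already carry part of the information. The conclusion assumes a linear model, scores that are close to complete, and scores computed from data recorded before randomisation.

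Three stronger readings are not supported. The omission does not bias any arm comparison. It does not undermine the stated 72 or 99 per group. It also does not show a fault in the missing-data plan.

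**What to change.** In the Statistical analysis plan section, add one continuous admission severity score, APACHE-II or SOFA but not both, to the pre-specified covariates for the aim 2 patient delirium outcomes. State that the admission value is used. Make the change before the outcome data are examined by arm.

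Using the same score as an auxiliary variable in any multiple imputation is optional.

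The cost is one line of wording and one degree of freedom. No new data collection and no change to the sample size are needed.

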#### Secondary aims

To determine the effect of family-administered delirium prevention, detection, and management in critically ill patients on family member symptoms of psychological distress, compared to usual care.To determine the effect of family-administered delirium prevention, detection, and management on the prevalence (ever/never delirium as indicated by an Intensive Care Unit Delirium Screening Checklist [ICDSC] score ≥ 4), duration (total days of an ICDSC score ≥ 4), and severity of delirium (as indicated by the ICDSC score, which ranges from 0 to 8) in critically ill patients, compared to usual care.To determine the effect of family-administered delirium prevention, detection, and management on the diagnosis of the patient with delirium (ICDSC score ≥ 4), compared to usual care.To determine the effect of family-administered delirium prevention, detection, and management on family member knowledge of delirium in critically ill patients, compared to usual care.To determine the effect of family-administered delirium prevention, detection, and management on the burden of delirium (e.g., feelings of helplessness) experienced by family members of critically ill patients, compared to usual care.

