##### Kessler Psychological Distress Scale (K-10) (secondary aim 1)

The K-10 is a 10-item tool to measure psychological distress and the likelihood of having a mental disorder [55] with higher scores indicating greater psychological distress. The questionnaire will be completed by caregivers (assessing their symptoms) once daily for up to five study days, and at 1-month and 3-month follow-up post patient ICU discharge.

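### Secondary aim 1 reports K-10 distress only as a proportion above an unstated cut; the baseline-adjusted mean would use the same data better at no cost

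*Protocol article*

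**What the plan says.** The Statistical analysis plan section of the protocol article gives one result for secondary aim 1: "A difference in proportion of the most severe family members symptoms of psychological distress [K-10"], assessed "at discharge from ICU, 1-, and 3- month follow-up) between control and intervention groups". No mean K-10 appears.

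Other parts of the article bear on this choice:

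- Under Secondary aims, the target is the effect "on family member symptoms of psychological distress, compared to usual care". It is not limited to severe distress.
- The K-10 paragraph under Measurement of outcomes describes a 10-item tool "with higher scores indicating greater psychological distress". It states no cut-off, whereas the GAD-7, PHQ-9 and ICDSC paragraphs each state one.
- For the primary scales, the analysis section lists proportions and also "mean PHQ-9 and GAD-7 scores, and frequency of categories of depression and anxiety". CIDKQ and DEL-B are listed as means.
- Table 2 schedules the K-10 at baseline, and the listed covariates include "baseline levels of symptoms of depression, anxiety, and psychological distress".
- The Abstract states: "All analyses will be intention-to-treat and adjusted for pre-identified covariates".
- The significance rule for all analyses is a "two-tailed *p*-value < 0.05 to be statistically significant".

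**The concern.** The stated analysis turns a graded score into a yes/no outcome and offers nothing else for this aim. Everyone on the same side of the cut is treated alike, so a fall in distress counts only if it carries a family member across the line. If few controls lie above the line, few events remain to compare.

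The K-10 is the only one of the five family outcome scales without a reported mean, and nothing in the aim calls for that. At stake is the precision of the answer on psychological distress: a real shift of moderate size is more likely to be missed than it need be. Because the article leaves the cut open, it also does not say which contrast will be tested. A missing cut-off alone could be left to a fuller plan. The choice of a proportion as the sole listed result is a stated method, and it can be improved.

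**Working it through.** **The plan's own figures.** No calculation is given for the K-10. The two stated sample sizes supply the number evaluable and an effect size to borrow.

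- Primary: difference 3, SD 5, 90% power, two-sided 0.05. n = 2 × (1.960 + 1.282)² × 5² / 3² = 58.4, so 59 per group (60 by the t-test). 60 × 1.2 = 72, the stated figure; 59 / 0.8 = 73.75, so 74. The stated 72 is reproduced to within rounding and the way loss is applied.
- Secondary: 10% against 30%. The unpooled formula gives (1.960 + 1.282)² × (0.09 + 0.21) / 0.20² = 78.8, so 79 per group, and 79 / 0.8 = 98.75, so 99. The pooled formula gives 82, and 82 × 1.2 = 98.4, so 99. The stated 99 is reproduced.
- Evaluable per group: 99 × 0.8 = 79.2, taken as 79.

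**Assumptions not in the documents.** K-10 scores are normal with equal SD in both arms. The intervention shifts the whole distribution by d SD units, with d from 0.4 to 0.6. The upper value is the 3/5 planned for PHQ-9 and GAD-7; the documents give none for the K-10. The share p of controls above the cut is unknown and is varied from 5% to 50%.

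**Information kept by the split,** relative to the unadjusted mean: φ(z_p)² / [p(1 − p)], where z_p cuts off the upper share p. At p = 0.10, φ(1.282) = 0.1755, so 0.1755² / 0.09 = 0.342. At p = 0.50, 0.3989² / 0.25 = 0.637.

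**Power of the split.** The intervention-arm share is p₂ = 1 − Φ(z_p + d). Power comes from the pooled two-proportion test with 79 per group. At p = 0.10 and d = 0.6, p₂ = 1 − Φ(1.882) = 0.030, or about 8 against 2 events, and power is 0.43.

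**Power of the mean.** Unadjusted t-test with 79 per group.

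| Controls above cut | Information kept | Power, d = 0.4 | Power, d = 0.5 | Power, d = 0.6 |
|---|---|---|---|---|
| 5% | 0.22 | 0.17 | 0.22 | 0.27 |
| 10% | 0.34 | 0.25 | 0.34 | 0.43 |
| 15% | 0.43 | 0.32 | 0.43 | 0.55 |
| 20% | 0.49 | 0.37 | 0.50 | 0.63 |
| 30% | 0.58 | 0.44 | 0.60 | 0.74 |
| 50% | 0.64 | 0.51 | 0.69 | 0.84 |
| Unadjusted mean | 1 | 0.70 | 0.88 | 0.96 |

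**Baseline adjustment.** If baseline and follow-up K-10 correlate at 0.5 (an assumption), the adjusted mean has power 0.83, 0.95 and 0.99 at d = 0.4, 0.5 and 0.6. Adjusting the proportion for baseline recovers little. In simulation at d = 0.5 (2000 runs per setting), the unadjusted proportion has power 0.36, 0.53 and 0.60 at p = 10%, 20% and 30%; the adjusted proportion has 0.37, 0.57 and 0.66. The loss therefore comes from the cut, not from a lack of adjustment.

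**The case against.** A reader might infer that the plan throws away most of the power for this aim, or that a real effect would probably be reported as no difference. The documents do not support either as a general statement. At 0.6 SD, power falls by more than half only if about 10% or fewer of controls are above the cut. At 15% it is 0.55 against 0.96. The chance of a significant result drops below one half at up to about 10% above the cut for 0.6 SD, and at just under 20% for 0.5 SD. Nothing in the article says that severe distress is that rare. The sample size section assumes a control mean of 13 (SD 5) on PHQ-9 or GAD-7, above their threshold of 10, so this is a highly symptomatic group. By analogy only, a cut placed like that has 1 − Φ(−0.6), or about 73%, of controls above it; at 0.6 SD the split would then have power of about 0.84.

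Other points on that side also stand. The phrase *most severe* is ambiguous. For the ICDSC, the same section uses those words of scores, and for the K-10 they might mean each family member's worst daily score, although that fits the 1- and 3-month assessments less well. The effect size is borrowed from other scales. An effect confined to the severe tail would lose less. Baseline adjustment is already planned, so its absence cannot be held against the plan. Finally, this is one secondary outcome that does not drive the sample size, and it sits beside two primary scales that are reported as means.

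None of this supplies a reason to leave out the mean. Under a uniform shift, even the most favourable cut keeps only 64% of the information.

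**Conclusion.** The point holds in a limited form. The only result listed for secondary aim 1 is a proportion above an unstated cut, although the aim is general, the score is graded and the other family scales have means.

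Under normal scores, a uniform shift and 79 evaluable per group, the split always loses precision. It keeps less than half of the information if about 20% or fewer of controls are above the cut, and at most about 64% at any cut. The cost in power ranges from modest (0.84 against 0.96) to severe (0.17 against 0.70), depending on a severe rate and an effect that the documents do not give.

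This is a free improvement to a secondary analysis. It is not an error that threatens the trial's primary conclusion.

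**What to change.** In the Statistical analysis plan section, make the main analysis of secondary aim 1 the between-arm difference in mean K-10 at ICU discharge, 1 month and 3 months, from a linear regression adjusted for baseline K-10. Keep the proportion as a supporting description. State before the data are examined what *most severe* refers to (a score band, or each person's worst score) and which cut-off applies.

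The cost is a sentence or two of text. The K-10 is already scheduled at baseline and follow-up, and baseline distress is already a listed covariate. Sample size, assessments and burden on families do not change.
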